## Methods

### Objectives and design

The primary hypothesis for this study is that bupivacaine injection before neurolysis dilutes the neurolytic effect of alcohol and therefore decreases its analgesic effectiveness. We also believe that bupivacaine injection has no influence on intra- or immediate post-procedural pain.

The primary aim of study is to compare the effectiveness of EUS-CPN with and without bupivacaine. Secondary aims include a comparison of intra- and post-procedural pain, narcotic use, adverse events, and survival between the studied groups.

This is a single-center, randomized, double-blinded, parallel groups, non-inferiority clinical trial to be performed at the endoscopy unit of the Centre Hospitalier de l’Université de Montréal (CHUM) in Québec, Canada.

The SPIRIT reporting guidelines have been used in protocol formulation [9].

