## Outcomes

### Primary outcome

Comparative change in Likert pain scores before procedure (T0) and at 30 days after the procedure (Table 2) with treatment failure defined as less than 3-point decrease in Likert pain scores.

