### Secondary outcomes

% Difference in 7-point Likert scale and GRSC (Table 2):T0 and all other time points specified aboveTime to discharge from the endoscopy unit% Change in cumulative narcotic use for the previous 3-day period:T0 vs T60 daysT0 vs T120 daysRate of all intervention-specific adverse events (Using the American Society of Gastrointestinal Endoscopy classification) [10]Survival

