### Statistical analysis

Descriptive statistics will assess patient characteristics (demographics, tumor size) and the balancing of randomization. The data will be tested for normality, and the paired Wilcoxon ranked sum test will assess the pain scores. Student’s *t* test will be performed when comparing two means. Fisher’s exact method will be used for proportions comparison. All *p*-values are two-tailed, and values < 0.05 will be considered statistically significant. Subsequent logistic regression modeling will determine the factors that are associated with a better pain outcome.

Kaplan-Meier estimates of the survival curve will be obtained for each treatment group, and statistical comparisons of these will be performed using the log-rank test. The Cox proportional hazards models will be used to study survival while adjusting for potential confounding factors.

Patients who withdraw will be noted and will be noted and they will be excluded from analysis.

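### The test assigned to the pain scores is misnamed and called paired, which does not fit a comparison of two parallel arms

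*Protocol article*

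**What the plan says.** The Objectives and design section gives the primary aim as to "compare the effectiveness of EUS-CPN with and without bupivacaine", in a parallel-group trial. The Primary outcome section defines the outcome as "Comparative change in Likert pain scores before procedure (T0) and at 30 days after the procedure", with "treatment failure defined as less than 3-point decrease in Likert pain scores". The Sample size calculations section is built on a difference between the two groups.

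The Statistical analysis section then states that the data will be tested for normality and that "the paired Wilcoxon ranked sum test will assess the pain scores". It goes on to say that Student's t "test will be performed when comparing two means" and that "Fisher’s exact method will be used for proportions comparison". It adds: "Subsequent logistic regression modeling will determine the factors that are associated with a better pain outcome". The Wilcoxon sentence is the only one that ties a named test to the pain scores. The t test is not described as paired or unpaired, and treatment arm is not named as a factor in the logistic model.

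The Secondary outcomes section frames the further pain comparisons as "T0 and all other time points specified".

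**The concern.** The test's name joins two incompatible procedures. The word *paired* points to the signed-rank test, which asks whether patients' scores moved between two visits. The words *ranked sum* point to the two-sample test, which asks whether one group's values tend to exceed the other's. Only the second addresses the trial's question.

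An analyst who follows *paired*, and sees outcomes expressed as T0 against a later time, would run a before-after test inside each arm. That produces no estimate, interval or p-value for bupivacaine against no bupivacaine. Both arms receive 20 mL of absolute alcohol (Study arms), and the Background treats the procedure's effectiveness as established. The likely result is two small p-values, which could be misread as showing that the arms perform alike. That misreading is easier in a trial labelled non-inferiority.

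**Working it through.** **1. What kind of comparison was the trial sized for?** The article writes n = 2 × 7.8 × (7/3)² with a difference of 3, SD 7, alpha 5% and power 80%.

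- With the article's rounded factors: 2 × 7.8 × 5.4 = 84.2. With (7/3)² = 5.44: 84.9.
- With the unrounded multiplier 7.849: 2 × 7.849 × 5.444 = 85.5, so 86 per group.
- The stated 90 is not reproduced exactly. The excess is on the safe side and is not the point here.

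What matters is the leading factor 2, which comes from the variance of a difference between two independent means. A paired formula, (z_α/2 + z_β)² × (SD/δ)², has no such factor. The trial was sized for an unpaired comparison.

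**2. The relevant statements side by side.**

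| Place in the protocol article | Comparison implied |
|---|---|
| Objectives and design, primary aim | Between arms |
| Objectives and design, parallel groups | Unmatched arms |
| Sample size calculations | Between arms, independent groups |
| Primary outcome, comparative change | Between arms, on change from T0 |
| Statistical analysis, test for pain scores | *Paired* (within patient) and *ranked sum* (between groups) at once |

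Four entries agree. The fifth contradicts itself, and its paired half contradicts the other four.

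**3. What a within-arm paired test would show.** The article gives no usable SD for the change on the 0 to 6 scale, so these inputs are assumptions: baseline mean 4.3, baseline SD 1.1, follow-up noise SD 1.5, scores rounded and limited to 0–6, 90 per arm.

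A rough check, ignoring rounding and limits:

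- Within an arm, the SE of the mean change is 1.5/√90 = 0.158. A 1-point fall gives z = 1/0.158 = 6.3, and a 2-point fall gives z = 12.6. Both are far beyond 1.96.
- Between arms, the SE is 1.5 × √(2/90) = 0.224. A 1-point difference gives z = 1/0.224 = 4.5, and no difference gives an expected z of 0.

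Simulation under the same inputs, 2000 runs, two-sided 5%:

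| Mean fall, arm 1 / arm 2 | Both paired Wilcoxon tests significant | Unpaired t on change | Unpaired rank-sum on change | Fisher on treatment failure |
|---|---|---|---|---|
| 2 / 2 | 100% | 4.8% | 5.0% | 4.0% |
| 2 / 1 | 100% | 99% | 99% | 84% |

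The paired column is the same in both rows, so it does not separate equal arms from unequal ones. The unpaired tests do.

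**4. Sensitivity to the assumed distribution.** With SD 1.8 at each visit, correlation 0.5 and baseline means from 3 to 4.5, true falls of 1.2 against 2.0 left both paired tests significant in practically every run. The unpaired rank-sum test on change detected the difference in 69% to 84%.

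**The case against.** The strongest reply is that *paired* is a slip. *Ranked sum* is the usual name of the two-sample test, and everything else in the article points to a between-arm analysis. Expressing outcomes as change from T0 is the normal input to such an analysis and prescribes no within-arm test. The article is also condensed, and the choice of deciding test is commonly left to a statistical analysis plan that is not shown. Much of this stands: a wording error is at least as plausible as a plan to run only before-after tests. It does not remove the point, because the sentence is printed, contradicts itself and concerns the primary outcome. That is a misstatement, not a detail left out.

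Three stronger readings are tempting, and the document supports none of them.

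- *The plan never tests bupivacaine against no bupivacaine.* The same section names Student's t test for means and Fisher's exact test for proportions. Treatment failure is a proportion inside the primary outcome, and Fisher's test on it by arm is a valid between-arm test.
- *The normality test decides whether the t test is used.* The article says that normality will be tested but does not make the t test depend on the result. The stated condition is only that two means are compared.
- *Identical arms would often appear to differ because one before-after test is significant and the other is not.* With SD 1.8 and correlation 0.5, the two paired tests disagree in about 40% to 54% of runs when both arms fall by only 0.3 to 0.5 points. This drops to roughly 10% at 0.75 points, under 1% at 1 point, and none at 1.5 to 3 points. The protocol counts any fall below 3 points as failure, so the small falls are remote from what it plans for. Nor does it say that an arm effect would be inferred from two separate p-values.

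**Conclusion.** The point holds as an error in a stated analysis: the one test assigned to the pain scores has a contradictory name, and its paired reading cannot answer the primary question. That follows from the text and needs no assumption.

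The consequence is conditional. If the sentence were followed as paired, with falls of about 1 point or more in each arm and SDs in the range tried, both tests would be significant in practically every trial of this size whatever the arm difference. The exact percentages rest on assumed distributions and are illustrative. No error rate can be attached to the trial itself, because the article states no rule for turning within-arm results into a conclusion about the arms.

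Valid between-arm tests are named in the same section. What is missing is the express link from one of them to the pain scores, and the link that is printed is wrong.

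**What to change.** Delete *paired* and replace the sentence with wording such as: *The change in Likert score from T0 to day 30 will be compared between the randomised arms with the unpaired (two-sample) Wilcoxon rank-sum test, and reported with the between-arm difference and its 95% confidence interval. The proportion with treatment failure (a decrease of less than 3 points) will be compared between arms with Fisher's exact test. Any before-after tests within an arm are descriptive only.* Use the same between-arm form for the pain scores at the secondary time points.

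The rank-sum test keeps closest to the printed name. An unpaired t test on change would also be valid and performed the same in the check above, so what matters is that the named analysis is unpaired and fixed in advance.

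The cost is a few lines of text, with no change to data collection, patients or sample size. The article reports 36 patients recruited and recruitment continuing, so the correction can be made before the final analysis. It does not settle the non-inferiority label, for which the article states no margin. That is a separate matter.

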### Study population

All patients referred for EUS for suspected pancreatic malignancy or for neurolysis for pain due to proven pancreatic malignancy are eligible. The study will be presented to them by a single research assistant, who will also obtain study consent before the procedure. Patients will be randomized if they meet all inclusion criteria and have no exclusion criteria presented in Table 1.

**Table 1 Tab1:** Inclusion and exclusion criteria for the study

**Inclusion criteria**	1. Malignant-appearing pancreatic mass, or proven pancreatic cancer involving the pancreatic genu, body, or tail on imaging done before the endosonography 2. Any level of abdominal or back pain considered to be potentially related to the mass: a. New onset pain (< 3 months) b. Constant c. Centrally located d. With or without irradiation to the back e. No obvious other source of pain 3. No possibility of immediate surgical management. (Based on EUS evidence of venous involvement ≤ 1 cm from portal confluence and/or arterial involvement of the celiac axis or the splenic artery ≤ 1 cm from the bifurcation of the celiac axis, and/or evidence of liver metastases) 4. Signed, informed consent 5. Celiac axis accessible for *bilateral* neurolysis at EUS
**Exclusion criteria**	1. Allergy to bupivacaine 2. Tumors amenable for curative resection 3. Significant coagulopathy (platelets < 50000 µ/L, INR > 1.4, uninterrupted use of oral anticoagulants at therapeutic dosage [except for antiplatelet agents] 4. Patients with concurrent sepsis 5. Previous EUS CPN

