### Duration

Approximately 3000 EUS procedures are performed at CHUM annually, including approximately 300 adenocarcinomas of the pancreatic genu/body/tail, of which 90% (270) are inoperable and have pain. Given a sample size requirement of 90 patients and allowing for a 50% refusal/dropout rate, this study could be completed in approximately one and a half years. This was the approximate time frame for our previous RCT on neurolysis in the same patient population [4]. An extra 3 months will be necessary for completion of data analyses and drafting of the manuscript. The study will be terminated as soon as recruitment is complete. An extension will be requested if recruitment is not complete after one and a half years.

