### Randomization and blinding

Participants will be randomized in 1:1 fashion, by sealed opaque envelopes, prepared by an independent third party, using a list produced by the web-based randomization service Sealed Envelope™.

Since the final inclusion criteria (accessibility of the celiac axis by EUS) is determined during the procedure, while the patient is sedated, the patient will be blinded to the treatment arm.

The research nurse who collects the data will not be present during the randomization process, nor the procedure, and will therefore also be blinded to the treatment arm.

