### Patient follow-up

Patients will be followed in the immediate post-procedural period until 4 months after the procedure or death whichever comes first; see Fig. 1.

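### Read literally, the withdrawal rule discards outcomes observed before withdrawal and drops withdrawn patients from the survival analyses instead of censoring them

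*Protocol article*

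**What the plan says.** The rule is the last sentence of the Statistical analysis section in the protocol article: "Patients who withdraw will be noted and will be noted and they will be excluded from analysis". It comes directly after the survival paragraph, which states that "Kaplan-Meier estimates of the survival curve will be obtained for each treatment group", with a log-rank comparison, and that "The Cox proportional hazards models will be used to study survival while adjusting for potential confounding factors".

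Other sections that bear on it:

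- **Primary outcome:** change in Likert pain from T0 to day 30, "with treatment failure defined as less than 3-point decrease in Likert pain scores".
- **Patient follow-up:** patients are followed "until 4 months after the procedure or death whichever comes first". Calls are scheduled at days 3, 7, 30, 60, 90 and 120, so three of the six come after the primary time point.
- **Secondary outcomes:** these include adverse events and survival.
- **Study population, and Randomization and blinding:** the research assistant is the person "who will also obtain study consent before the procedure", while access to the celiac axis, the last inclusion criterion, "is determined during the procedure, while the patient is sedated".
- **Duration:** recruitment time is planned "allowing for a 50% refusal/dropout rate".

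The article nowhere mentions an intention-to-treat set, censoring at withdrawal, or use of data given before withdrawal.

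**The concern.** This is a stated rule and not a detail left to a fuller document. An analysis plan that follows it inherits it.

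The treatment is a single procedure, so a patient who later leaves telephone follow-up has still received the allocated treatment in full. Removing that patient corrects no treatment deviation, and the non-inferiority label therefore gives no per-protocol reason for it. What is lost is observed data: a day-30 score if withdrawal comes later, earlier pain scores and adverse events if it comes sooner, and survival time up to the date of leaving.

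Two comparisons are at stake. For pain, if patients with poor relief leave more often in one arm, that arm looks better than it is. For survival, a patient must be alive to withdraw, so exclusion removes only people known to have survived for a time, and the arm with more withdrawals looks worse than it is.

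**Working it through.** **1. The plan's own figures.** The article gives no withdrawal rate and no figure for the effect of the rule. The nearest number is the sample size. Its printed product is 2 × 7.8 × 5.4 = 84.2 (84.9 with (7/3)² unrounded), against 90 per group stated. That mismatch is a separate matter, and nothing below depends on it.

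**2. What the rule does by date of withdrawal, for a randomised and treated patient.**

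| Withdrawal | Known by then | Under the rule |
|---|---|---|
| Between day 7 and day 30 | Scores at T0, days 3 and 7; adverse events; alive to that date | All removed |
| After day 30, e.g. day 70 | Also the primary outcome | All removed |

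**3. Failure at day 30 (assumed rates).** Let p be true failure, and w_f and w_s the proportions of failures and successes who withdraw. Failure among those left is p(1 − w_f) / [p(1 − w_f) + (1 − p)(1 − w_s)].

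- p = 0.50, w_f = 0.30, w_s = 0.10: 0.35 / (0.35 + 0.45) = 43.75%.
- p = 0.50, w_f = 0.10, w_s = 0.10: 0.45 / 0.90 = 50.0%.
- Spurious difference: 6.25 points, with 20% withdrawn in one arm and 10% in the other.
- With p = 0.30: 0.21 / 0.84 = 25.0% versus 30.0%, a difference of 5.0 points.
- With the same w_f and w_s in both arms and equal true failure, the difference is zero.

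**4. One-arm worst case for the mean.** If exactly the worst fraction q of a normal distribution leaves one arm and nobody leaves the other, the mean of the first moves by φ(z₁₋q)/(1 − q) SD: 0.11 for q = 5%, 0.195 for 10%, 0.35 for 20%. This is a bound and not an expectation.

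**5. Survival (assumed exponential, median 6 months, withdrawal independent of death).** True 4-month survival is 0.5^(4/6) = 0.630. Simulation with 400,000 patients per setting gave:

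| Underlying 4-month withdrawal | Actually withdrawn | Censored | Excluded |
|---|---|---|---|
| 10% | 8.0% | 0.631 | 0.617 |
| 20% | 16.2% | 0.630 | 0.601 |
| 30% | 24.2% | 0.629 | 0.582 |

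Hand check of the last row: those left who survive 4 months are 0.630 × 0.70 = 0.441 of all patients, and those left are 1 − 0.242 = 0.758, so 0.441 / 0.758 = 0.582. For assumed medians of 4 to 9 months the loss runs from 1.1 points (0.735 to 0.724) to 5.1 points (0.500 to 0.449).

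With identical true survival and withdrawal of 30% versus 10%, the death-rate ratio is 1.12 under exclusion and 0.995 under censoring. A control run with 10% in both arms gave 0.989 and 0.988, so simulation error is about 0.01.

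**6. Why power is left out.** Normal-approximation power is Φ[(3/SD)√(n/2) − 1.96]. With the printed SD of 7 it is 82% at n = 90, 78% at 81 and 73% at 72. But the scale in Table 2 runs from 0 to 6, so a change score lies between −6 and +6 and its SD cannot exceed 6. At SD 6 and n = 72 (20% excluded): 0.5 × 6 − 1.96 = 1.04, which is 85%.

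**The case against.** Four objections deserve an answer.

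- **The scope is read in.** The sentence does not say every analysis, nor after randomisation. It is loosely drafted and repeats itself. Since consent precedes the procedure and eligibility is completed during it, some withdrawals may come before randomisation, and leaving those out is legitimate. This stands as a caution: a reader might infer that the authors deliberately chose to drop withdrawn patients from the survival curves, and the text does not show that intent. It does not remove the point, because nothing limits the rule to early withdrawals or exempts any analysis.
- **The bias may be small or absent.** Patients and the data collector are blinded, death ends follow-up separately from withdrawal, and equal withdrawal patterns with equal true failure give no bias in the failure comparison. All of this stands. That withdrawal follows poor pain relief is plausible but is not in the article. A reader might take the 0.11 to 0.35 SD shifts as likely effects, but they need all the worst responders to leave one arm and none the other.
- **Power.** A reader might infer that exclusions push the trial below 80% power because the formula has no dropout allowance. The article does not support this. The calculation needs an SD that the scale cannot produce, and the stated 90 is already about 7% above the printed product (90 / 84.2 = 1.07). The 50% figure in Duration combines refusal with dropout and serves only recruitment time, so it cannot be read as a withdrawal rate. Whether withdrawn patients are replaced is not clear.
- **Prescribing a model.** Replacing the planned tests with a mixed model would go beyond the defect, and none is asked for.

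**Conclusion.** The point holds in this form: the rule is wrong as written, because taken literally it discards outcomes already observed and handles withdrawal in the survival analyses by deletion where censoring applies. It touches the primary comparison, adverse-event rates and survival.

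The actual size cannot be stated, because it depends on withdrawal rates, and their relation to outcome and arm, which the article does not give. Under the assumed rates above, the distortion is 5 to 6.25 percentage points in the failure comparison and about 1 to 5 points in 4-month survival within an arm. For failure, bias between arms that truly do not differ requires withdrawal that both relates to outcome and differs by arm. For survival, a difference in withdrawal rates is enough, because exclusion itself ties removal to having stayed alive. No conclusion about power is drawn.

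**What to change.** Replace the sentence with wording such as:

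> All randomised patients are analysed in their allocated arm using all data collected up to withdrawal. A patient with a day-30 score is included in the primary analysis regardless of later withdrawal. Survival is censored at the date of withdrawal. Patients who withdraw before day 30 without a score are counted as treatment failures in a sensitivity analysis.

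Keep the analysis that excludes withdrawals only as a further sensitivity analysis. Data given before withdrawal stay in unless the patient refuses their use. The main-analysis handling of a patient with no day-30 score still needs one stated rule, which can sit in the statistical analysis plan.

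The cost is a wording change, submission to the ethics board as the Trial status section provides, and a little more analysis. The scores are already scheduled. The limit is that censoring is unbiased only if withdrawal is non-informative, so reporting the number, timing and reasons of withdrawals by arm is worthwhile. The change should be made before unblinding.

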## Trial status

The CRCHUM Research Ethics Board (REB), more precisely its CT2 Panel, has reviewed this research project at its full board meeting where quorum was reached. It was approved, with number of 2022-9969, 21.151. Approval was communicated to the principal investigator on September 21, 2021. No REB member withdrew from the deliberations. Any protocol modification will be submitted to the REB. We have started recruitment on November 2, 2021, and 36 patients have been recruited to date. The recruitment is expected to continue until the target sample size is reached.

